**RIVER Feasibility, Acceptability, and Satisfaction (Aim 2)**		
Feasibility	Extent of how workable, possible, doable, and easy RIVER was	Feasibility Intervention Measure (FIM)
Acceptability	Extent of how agreeable, palatable, or satisfactory RIVER was	Acceptability of Intervention Measure
Satisfaction	Assesses RIVER on quality, needs met, and helpfulness	Client Satisfaction Questionnaire
**Distal & Proximal Outcomes (Aim 3)**		
Grief Symptoms (Primary)	Presence and extent of persistent emotional, cognitive, and behavioral responses to the loss by the griever (e.g., intense yearning, preoccupation with the deceased, difficulty accepting the death, and disruptions in daily functioning)	Brief Grief Questionnaire (BGQ)
Connectedness	Extent to which individual still feels bonded to their deceased loved one and the people in their community	Continuing Bonds Scale Multidimensional Scale of Perceived Social Support\
Grief Acceptance	Presence and extent of adaptive beliefs that support the griever in acknowledging the loss, tolerating painful emotions, maintaining a meaningful connection with the deceased, and re-engaging in their daily life	Typical Beliefs Questionnaire
Coping Strategies	Cognitive, behavioral, social, and spiritual tools the griever uses to manage the emotional, practical, and existential challenges that arise after a loss	The Coping Assessment for Bereavement and Loss Experiences (CABLE)
Grief-related Avoidance	Presence and extent of efforts used by the griever to evade external and internal reminders of the loss (e.g., certain places, activities, thoughts, or emotions about the deceased) and reduce distress	Grief-Related Avoidance Questionnaire (GRAQ)
**Secondary Outcomes (Aim 3)**		
Substance Use	Presence and frequency of substance use, and substance use disorders in the past 30 days	Tobacco, Alcohol, Prescription Medication, and Other Substances Tool (TAPS) PROMIS
Depression	Presence and severity of symptoms related to Major Depressive Disorder (e.g., persistent sadness, anhedonia, changes in sleep and appetite, and suicidal ideation)	Patient Health Quesitonnaire-9 (PHQ-9)
Posttraumatic Stress Disorder	Presence of certain experiences related to the loss by the griever (e.g., nightmares about the loss, avoidance of reminders of the loss, hypervigilance, emotional or social detachment, and guilt or blame about the loss) over the past month that are associated with posttraumatic stress disorder	Primary Care PTSD Screen for DSM-5 (PC-PTSD-5)
Physical Pain	The intensity of physical pain experienced by the griever and the level of interference on their daily life and wellbeing	Pain, Enjoyment of Life and General Activity Scale (PEG)
**RIVER Peer Grief Ally Outcomes (Aim 3)**		
Grief Symptoms	Presence and extent of persistent emotional, cognitive, and behavioral responses to the loss by the griever (e.g., intense yearning, preoccupation with the deceased, difficulty accepting the death, and disruptions in daily functioning)	Brief Grief Questionnaire (BGQ; same measure used in the primary outcome with grievers)
Posttraumatic Growth	Presence and extent of positive psychological changes following overdose bereavement that reflect a greater appreciation of life, improved relationships, increased personal strength, and an openness to new possibilities	Posttraumatic Growth Inventory (PTGI)
Burnout	Presence and extent of physical and emotional exhaustion as a result of prolonged stress and work demands that is characterized by fatigue, reduced energy, and diminished motivation	Copenhagen Burnout Inventory

**Fig. 3 Fig3:**
[figure not shown]
Hypothesized outcomes

### Data management and analysis plan

Aim 3 will test the effect of receiving the RIVER peer grief support model plus EUC compared to EUC alone by contrasting outcomes of grief and using regression-based modeling to leverage all time points while adjusting for the stratification variable. We will use Intent-to-Treat analyses. Hypotheses regarding the effectiveness of the RIVER peer grief support approach will be tested with a repeated measures mixed-effects linear model, with experimental group, time (4 assessment time points), and their interaction as fixed effects. Inclusion of the interaction term will allow for examination of the difference in response trajectories between intervention arms. We will also include the stratification variable as a covariate in the model. For missing data, we will proceed with likelihood-based mixed-effects models, which are valid under the Missing at Random (MAR) assumption. For non-ignorable missingness, we will add sensitivity analyses. Qualitative interview data with peer grief allies will also be used to contextualize quantitative results. For example, if allies share that support was more or less challenging for certain groups, we may explore potential moderators of the treatment effect.

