**Fig. 2 Fig2:**
[figure not shown]
Pilot and RCT study design

Next, the study team will engage potentially eligible grievers. We will contact grievers to describe the study, screen them for eligibility, conduct the informed consent process, gather baseline data, and send the psychoeducational materials and list of local grief resources that make up EUC. The study team will contact families 30 to 90 days after they receive the death notification to contact grievers. This delay in outreach was recommended by PSCP and our advisory boards who suggested that grievers may be focused on making funeral arrangements and addressing immediate stabilization needs in the immediate aftermath of loss. However, grievers who contact the study team earlier may be enrolled earlier upon their request.

Enrolled participants will be referred to PSCP for peer grief support. PSCP will review grievers’ information and match them with a peer grief ally. Grievers are matched to an ally when possible, based on relationship to the descendent (e.g., parent vs. spouse) and geographical location (e.g., time zone). PSCP will contact the participant within three business days to schedule the first RIVER peer grief support session. During the first session, RIVER peer grief allies will schedule at least two additional sessions over the initial three months after enrollment at a cadence agreed-upon the peers and participants. All sessions will be conducted virtually or by phone. Sessions will be audio recorded to support peer grief ally supervision and fidelity assessment.

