### Aim 3 procedures

We will recruit people who are bereaved by overdose from our three partnering MEOs for an RCT comparing the RIVER peer grief model plus EUC to EUC alone. Participants will complete assessments at baseline and 3-, 6-, and 12-month follow up. The inclusion and exclusion criteria for the RCT will be identical to Aim 2 unless advised otherwise by the advisory boards. We aim to recruit 320 people with a goal of 65% retention (208 people) at the 12-month follow-up.

We will also recruit the RIVER peer grief allies (up to 10) to complete a baseline and follow-up survey prior to and after the RCT. They will also be invited for a brief qualitative interview post-RCT to assess their experiences delivering peer grief support.

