#### Randomization and stratification

Upon completion of the baseline survey, participants will be randomly assigned to the RIVER peer grief support model plus EUC or to EUC alone. Randomization will involve a stratified permuted block randomization with random size blocks. This ensures the number of people allocated to each group is approximately equal throughout recruitment [64]. We will stratify the sample by history of opioid misuse (lifetime heroin use and/or lifetime prescription opioid misuse) [65], under the premise that (1) drug overdose bereavement among PWUD may increase risk for future drug overdose deaths which typically involve opioids and (2) PWUD may experience grief problems that are more severe or different from people bereaved by a drug overdose death who do not use drugs. Randomization will be performed within each stratum.

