### Power

We powered our trial to detect a moderate effect size based on arm-differences of proportions of prolonged grief, due to the dearth of pilot data on mean differences. We considered an 18% arm difference in rates of prolonged grief symptoms, assuming 27% in the RIVER plus EUC arm and 45% in the EUC only arm. Since the RIVER peer grief support model has not yet been evaluated in those specifically bereaved by drug overdose deaths, we conservatively used estimates of proportions reported on rates of PGD among those bereaved by suicide [6]. We will have 80% power to detect a moderate effect size of a Cohen’s d of 0.4. We based this calculation on a two-tailed test of proportions for the null hypothesis of no difference in arms, and a significance level of 0.05. We are also adequately powered to perform repeated measures analysis to detect a group by time interaction term in a mixed model to address Aim 3. With our proposed follow-up sample size (*n* = 208), we have 90% power to detect a group by time interaction, expecting a Cohen’s d of 0.4 as before, and assuming adjustment of the baseline grief score, and a correlation of 50% between repeated measures.

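### The power figures make no allowance for differences between the up to 10 peer allies, and the model as described names no ally term

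*Protocol article*

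**What the plan says.** The analysis section of the protocol article (Data management and analysis plan) specifies a "repeated measures mixed-effects linear model, with experimental group, time (4 assessment time points), and their interaction as fixed effects", with the stratification variable added as a covariate. It does not list the random effects or the covariance structure.

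On delivery, the procedures say: "PSCP will review grievers’ information and match them with a peer grief ally". This stands under Aim 2, the pilot; Aim 3 describes no other way of assigning allies. Aim 3 gives their number: "We will also recruit the RIVER peer grief allies (up to 10) to complete a baseline and follow-up survey". EUC participants receive a booklet and a resource list and have no ally.

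On size: "We aim to recruit 320 people with a goal of 65% retention (208 people) at the 12-month follow-up". The randomisation section says that "the number of people allocated to each group is approximately equal throughout recruitment".

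The Power section claims 80% power for d = 0.4, "assuming 27% in the RIVER plus EUC arm and 45% in the EUC only arm", in a two-sided test at 0.05. At n = 208 it adds: "we have 90% power to detect a group by time interaction", with baseline adjustment and a correlation of 50% between repeated measures. That correlation is the only dependence it mentions. It gives no ally ICC, cluster size or design effect.

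**The concern.** RIVER is a way of relating to grievers rather than a fixed set of activities. The article plans to rate each ally's speech for fidelity and to coach allies individually every week. It is plausible that some allies will achieve more than others. Participants who share an ally then share part of their outcome, in the RIVER arm only. The variance of the RIVER mean has a component that shrinks with the number of allies, not with the number of participants, and there are few allies.

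At stake are the precision reported for the first controlled test of RIVER and the power on which the sample size rests. If the ally of each participant is not recorded during the trial, the matter may be impossible to repair afterwards.

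**Working it through.** **Inputs from the article.** 320 randomised and 208 at 12 months in about equal arms, so about 160 and 104 per arm; up to 10 allies; 27% against 45%; d = 0.4; two-sided alpha 0.05; baseline-adjusted with correlation 0.5. The article ties n = 208 expressly only to the 90% figure. I assume it also underlies the 80%, because 160 per arm would give 92% for the proportions.

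**Assumed.** The ally ICC, 0.01 to 0.10 (the article gives none), taken as a share of the variance in the analysis concerned; equal caseloads; 10 allies.

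**Step 1: the plan's own figures, all participants independent, 104 per arm.**
- Proportions, unpooled: SE = sqrt[(0.27×0.73 + 0.45×0.55)/104] = 0.0654. Then 0.18/0.0654 − 1.96 = 0.79, power 78.6% (77.6% with pooled variance).
- d = 0.4 unadjusted: 0.4/sqrt(2/104) − 1.96 = 0.92, power 82.2% (81.9% by noncentral t).
- Baseline-adjusted, residual variance 1 − 0.5² = 0.75: 0.4/sqrt(0.75×2/104) − 1.96 = 1.37, power 91.5%.

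These match the stated 80% and 90% to within about 2 points. No allowance for allies is hidden in them.

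**Step 2: partial nesting.** Caseload is 160/10 = 16 at randomisation and m = 104/10 = 10.4 at 12 months. The RIVER-arm variance is multiplied by DE = 1 + (m − 1)×ICC; the EUC variance is unchanged. The ratio of true to naive SE is sqrt[(DE + 1)/2].

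At ICC 0.05: DE = 1 + 9.4×0.05 = 1.47, and the SE ratio is sqrt(2.47/2) = 1.11.

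**Step 3: degrees of freedom.** By Satterthwaite, with 10 allies and 104 EUC participants, df = (DE + 1)²/[DE²/9 + 1/103]. At ICC 0.05: 6.10/(0.240 + 0.010) = 24.4. Power then comes from the noncentral t with noncentrality 0.4/sqrt[s²(DE + 1)/104], where s² is 0.75 adjusted and 1 unadjusted. At ICC 0.05 this is 3.00 adjusted and 2.60 unadjusted.

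| Ally ICC | DE | SE ratio | df | Adjusted power (stated 90%) | Unadjusted power, d = 0.4 (stated 80%) |
|---|---|---|---|---|---|
| 0.01 | 1.09 | 1.02 | 30.7 | 88.3% | 77.9% |
| 0.02 | 1.19 | 1.05 | 28.7 | 86.8% | 75.9% |
| 0.05 | 1.47 | 1.11 | 24.4 | 82.1% | 70.3% |
| 0.10 | 1.94 | 1.21 | 20.2 | 74.4% | 62.0% |

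Part of the loss comes from the few degrees of freedom. By normal approximation the adjusted powers are 90.2 / 89.0 / 85.0 / 78.4%.

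**Step 4: type I error of a test without an ally term.** 2×[1 − Φ(1.96/SE ratio)] gives 5.5 / 6.1 / 7.8 / 10.6%. This applies only when ally effects vary around an average of zero.

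**Step 5: number of allies.** Ten is a ceiling. With 6 allies and ICC 0.05, adjusted power is 73.0%. With 20 allies and ICC 0.05, the type I error in step 4 would be 6.2%.

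**The case against.** Several objections have force.

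- *The analysis model is not fully stated.* A reader might infer that the primary model ignores allies. The article lists fixed effects only, names no random effect even for participant, and is a condensed account; a fuller plan may contain an ally term. This stands: the article does not establish that the standard errors will be wrong. It does not rescue the power, which is stated as final figures and reproduces under independence.
- *Matching is not a cause.* The text says: "Grievers are matched to an ally when possible, based on relationship to the descendent (e.g., parent vs. spouse) and geographical location". A reader might take this as a source of inflated error. Participants are individually randomised, and sorting one arm by its own baseline traits adds no variance to that arm's mean. In simulations with 104 per arm, sorting on a prognostic trait and no ally effect, the within-ally ICC was 0.05 and 0.10, yet the naive test rejected in 4.9% and 5.2% of trials. This stands in full. Only variation caused by the allies counts.
- *Loss of the 5% level is not certain.* If RIVER has no effect through any ally, the ally variance is zero and 5% is held. Inflation needs allies whose effects differ and cancel on average. This stands.
- *The ICC is unknown.* At 0.01 the loss against the reproduced figures is about 1 to 3 points for the adjusted test and 2 to 4 for the unadjusted one. This stands, and it is why a range is needed.
- *The count of 10 comes from a survey.* It is given where allies are recruited to a survey. The wording reads as all RIVER allies, but more allies would reduce the effect.

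**Conclusion.** The point holds in a limited form. The stated power rests on independence of all 208 participants in a design where one arm is served by up to 10 allies. The described model names no ally term but does not exclude one. If allies differ in their effect, both stated powers are too high, and so is the precision from any model without an ally term.

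The size depends on an ICC that the article does not give. It is minor at 0.01 and material from about 0.05, where adjusted power is near 82% and unadjusted power near 70%. These figures assume 104 per arm, 10 allies, equal caseloads and the pilot's one-ally assignment carried into the RCT. The documents do not support saying that the 5% level is lost as a matter of course, or that matching inflates the error. This is something that should be fixed; it does not invalidate the trial.

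**What to change.** 1. Record the ally for every RIVER participant from the start of the RCT.
2. State a partially nested mixed model: a random ally effect on post-baseline outcomes in the RIVER arm only, EUC participants as singletons, and Kenward-Roger or Satterthwaite degrees of freedom.
3. Adjust that model for the matching variables (relationship to the decedent, and site). Otherwise the ally effect would absorb similarity due to matching, which does not belong in the standard error. Relationship is already listed among the potential covariates.
4. Report the estimated ally ICC.
5. Restate power over an ICC range of 0 to 0.10 at the planned number of allies, and confirm whether 10 is the total.

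The cost is wording, one identifier variable, a somewhat wider confidence interval and a less favourable stated power. No participants are added, so the change makes the power honest but does not restore it.

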### Aim 2 procedures

We will work with our three partnering MEOs to recruit 20 people bereaved by overdose for a pilot study of the RIVER peer grief support model (see Fig. 1). We will recruit one bereaved adult per decedent to participate in study assessments but, in keeping with PSCP’s inclusive practice, we will deliver the RIVER peer grief support model to other grievers who lost the same decedent upon request. We will offer study participation to the bereaved adult who the MEO obtains consent-to-contact, but remain flexible if that person feels another adult who is not the designated NOK would be a better fit for the study (e.g., someone who may benefit more from peer grief support). Participants will be people who (1) lost a loved one to an unintentional drug overdose death within the past year (2), are age 18 and older (3), fluently understand English or Spanish, and (4) have the capacity to give consent (e.g., excluding those with severe cognitive impairment, those in active psychosis, and those with developmental disabilities). Based on early feedback from our Medical Examiners Advisory Board, we will operationalize drug overdose deaths as those caused by intoxication from illicit substances (e.g., heroin), prescription substance misuse (e.g., using opioids in a way that was not prescribed), and/or counterfeit pills. Deaths in which intoxication exacerbated underlying medical conditions will be considered drug overdose deaths. Deaths that result from an adverse reaction to prescription medications that were used as prescribed (e.g., allergic reaction) will not be considered drug overdose deaths.

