The study will exclude people who (1) need hospitalization for psychiatric symptoms or substance use disorders (2), have active suicidal ideation (3), lost someone to a drug overdose death more than one year ago, or (4) lost someone to a drug overdose death that was suicidal in nature or of undetermined intent. Those who use substances but do not require hospitalization for substance use disorder will *not* be excluded given the connection between substance use and poor grief outcomes. We will include only those grieving death that occurred within the past year because prolonged grief disorder can be diagnosed no earlier than 12-months after a loss [55] and we aim to evaluate the effectiveness of the RIVER peer grief support model in preventing this outcome. On the recommendation of our advisory boards, we will exclude people bereaved by suicide and deaths of undetermined intent because the bereavement experiences of these populations differ from those bereaved by unintentional drug overdose deaths.

We will proactively recruit people bereaved by overdose from MEOs. MEOs routinely identify and contact the legal next-of-kin to overdose decedents in order to provide them with death notifications. At the participating MEOs, nearly all manner and cause of death rulings are complete within 60 days of receiving the decedents’ remains. After this determination, staff at our partnering MEOs will ask families bereaved by overdose to give consent to be contacted by the study team. MEO or study staff will provide grievers with a postcard that describes the study, provides a QR code that links grievers with a page with additional study details and a brief animation video describing the study (see Fig. 2). Study engagement procedures will be carried out by MEO staff including medical examiners, death investigators, and chaplains.

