#### Measures

All measures will be collected using surveys administered by an interviewer over the phone. We have selected measures that are reliable and valid in populations experiencing grief, as well as measures from the NIH HEAL Initiative Common Data Elements Repository and the NIH PhenX Toolkit [66] (see Table 1). Our primary outcome is PGD, and the associated outcomes that we are evaluating have previously demonstrated a relationship with the severity of grief symptoms experienced. We also have additional proximal and distal outcomes that will serve as pre-specified secondary outcomes (see Table 1; Fig. 3). Other potential covariates include participants’ relationship to the decedent, time since the death, history of exposure to other drug overdose deaths (i.e., number of people they knew who died by overdose), drug of choice (for PWUD enrolled in the RCT), and service utilization (measured using the NIH PhenX Access to Health Services Protocol derived from the National Health Interview Survey [67]).

**Table 1 Tab1:** Outcomes

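### PGD is the primary long-term outcome and is diagnosable only from 12 months after the loss, but the only effect named and powered in the mixed model for Aim 3 is a four-visit group-by-time interaction, with no 12-month contrast

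*Protocol article*

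**What the plan says.** - **Outcome.** The Measures section states "Our primary outcome is PGD", and Study aims lists PGD among the long-term outcomes. Table 1 marks grief symptoms on the Brief Grief Questionnaire as the primary row.
- **When PGD can be diagnosed.** Aim 2 procedures says that "prolonged grief disorder can be diagnosed no earlier than 12-months after a loss" and, of the same condition, that "we aim to evaluate the effectiveness of the RIVER peer grief support model in preventing this outcome".
- **Who enters and when.** Eligible people "lost a loved one to an unintentional drug overdose death within the past year"; Aim 3 procedures keeps these criteria for the RCT unless the advisory boards advise otherwise. On outreach, Aim 2 procedures says: "The study team will contact families 30 to 90 days after they receive the death notification".
- **Visits.** Aim 3 procedures: "Participants will complete assessments at baseline and 3-, 6-, and 12-month follow up".
- **Test.** Data management and analysis plan tests the effectiveness hypotheses with a linear mixed model containing group, time at four assessments and their interaction, and adds: "Inclusion of the interaction term will allow for examination of the difference in response trajectories between intervention arms".
- **Power.** The Power section starts from a comparison of two proportions. It then claims 90% power for the group-by-time interaction as the term that addresses Aim 3, with n = 208, d = 0.4, adjustment for baseline and a correlation of 0.5.

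**The concern.** The aim is about a condition that becomes diagnosable late. The one effect that the protocol names within its model and powers for Aim 3 is a difference in trajectories over all visits. An interaction over four categorical time points asks whether the arm difference changes anywhere. It gives an arm difference at 3 months the same weight as one at 12 months.

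Two things are at stake. A significant interaction could come wholly from early grief symptoms and leave the aim unanswered. And the power claim may belong to a different test from the one it is attached to, so nobody can tell from the text which test the trial was sized for.

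An early-only pattern is not far-fetched. At least three sessions are planned in the first three months (Aim 2 procedures), and meetings often thin out over time (RIVER peer grief model).

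**Working it through.** **Inputs from the protocol.** 208 people at 12 months with roughly equal allocation, so n = 104 per arm; d = 0.4; correlation ρ = 0.5; two-sided 0.05.

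**Assumptions of this check.** Compound symmetry, unit SD, complete data on 104 per arm, no arm difference at baseline, and the effect patterns below. The protocol gives no pattern over time. Effects are listed for baseline, 3, 6 and 12 months.

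**1. Timing.** Take notification as close to the loss and the pilot's outreach interval as carried into the RCT. Baseline then falls about 1 to 3 months after the loss, and the later visits at about 4 to 6, 7 to 9 and 13 to 15 months. The 12-month visit is past the threshold for everyone, because baseline follows the loss. The 6-month visit is past it only for those enrolled 6 months or more after the loss, and the 3-month visit only for those enrolled at 9 months or more. The one-year window permits both.

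**2. The stated 90%.** For one follow-up visit adjusted for baseline:
z = 0.4 / √[(1 − 0.5²) × 2/104] = 3.33; power = Φ(3.33 − 1.96) = 91.5%.
Without baseline adjustment: z = 0.4 / √(2/104) = 2.88; power 82.2%.
The adjusted single-visit contrast therefore reproduces the stated figure.

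**3. Interaction with categorical time (3 df).** The noncentrality is λ = (n/2)/(1 − ρ) × Σ(δₜ − δ̄)², and here (n/2)/(1 − ρ) = 52/0.5 = 104. Power is from the noncentral chi-square; a noncentral F gives 85.3% where this gives 85.6%.

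| Assumed effect | Σ(δₜ − δ̄)² | λ | Interaction significant |
|---|---|---|---|
| 0, 0.4, 0, 0 (3 months only) | 0.12 | 12.48 | 85.6% |
| 0, 0, 0, 0.4 (12 months only) | 0.12 | 12.48 | 85.6% |
| 0, 0.4, 0.4, 0.4 (sustained) | 0.12 | 12.48 | 85.6% |
| 0, 0.4, 0.4, 0 (gone by 12 months) | 0.16 | 16.64 | 94.3% |
| 0, 0.1, 0.2, 0.4 (building) | 0.0875 | 9.10 | 71.7% |
| 0, 0.2, 0, 0 (smaller, 3 months only) | 0.03 | 3.12 | 28.5% |

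For the first row, ρ = 0.3 gives 70.7% and ρ = 0.7 gives 98.0%.

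**4. Interaction with linear time in months (1 df).** Centred times are −5.25, −2.25, 0.75 and 6.75, with Σc² = 78.75. The SE of Σcδ is √[(1 − 0.5) × 78.75 × 2/104] = 0.870.
- 3 months only: Σcδ = −2.25 × 0.4 = −0.9, z = −1.03. Significant in 17.9%, nearly all with the slope opposite in sign to a growing benefit.
- Sustained 0.4: Σcδ = 5.25 × 0.4 = 2.1, z = 2.41, power 67.5%.
- Building 0.1/0.2/0.4: Σcδ = 2.625, z = 3.02, power 85.5%.

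**5. Baseline-adjusted 12-month contrast.** It is positive in 5% of trials when there is no 12-month difference, and in 91.5% when d = 0.4 at 12 months, whatever happens earlier.

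**The case against.** **The interaction is not called the single primary test.** This is correct. A reader might infer that the protocol fixes an omnibus interaction as its decision rule. The text does not say so: the sentence speaks of examining trajectories, the same section speaks of contrasting grief outcomes, and the Power section starts with two proportions. The named model can also deliver a 12-month contrast, and a full analysis plan may name one. What remains is that the article is not silent. It names one effect in the model for Aim 3 and claims power for it.

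**The large figure depends on categorical time.** This stands as a limit on the size. Four assessment time points read most naturally as categories, but the coding is not stated. With linear time the early-only figure is about 18%, and the building benefit has 85.5% power, above the 82.2% of an unadjusted 12-month contrast though below the 91.5% of the adjusted one. So the tempting claim that the interaction is always weaker than a direct contrast fails. Under a sustained effect the 3-df test (85.6%) also beats the unadjusted contrast.

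**The timing is not absolute.** A reader might infer that PGD cannot exist at the earlier visits. The protocol speaks of when it can be diagnosed, late enrollees may pass that point before the last visit, and no distribution of enrolment times is given.

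**An early effect need not be reported as preventing PGD.** The primary measure in Table 1 is a symptom questionnaire that can be scored at every visit. That an early result would be misreported is conjecture. That the named effect cannot separate early from late is not.

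**The authors may have meant a single-visit contrast.** The reproduction of the 90% suggests it. That makes this a matter of clarification more than of an invalid design.

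**Conclusion.** The concern holds at moderate severity. The stated aim needs an answer at or beyond 12 months after the loss, while the named and powered effect spans four visits and singles out none.

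If time is categorical, an assumed d = 0.4 at 3 months alone makes that effect significant in about 85% of trials, no less often than the same effect at 12 months alone. The figure falls to about 28% at d = 0.2. If time is linear, the early-only problem shrinks to about 18%, and the cost moves to power: 67.5% for a sustained effect against the 90% claimed. Under either coding, the claimed 90% is not what the interaction delivers for a sustained d = 0.4; it matches the baseline-adjusted contrast at one visit.

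These results rest on compound symmetry, complete data on 104 per arm, and effect patterns that the protocol does not supply.

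**What to change.** In Data management and analysis plan, name the between-arm difference at the 12-month visit, adjusted for baseline and estimated from the same mixed model with categorical time, as the primary test. In Power, attach the 90% statement to that contrast. Make the group-by-time interaction and the 3- and 6-month contrasts secondary, and report them as grief symptoms and not as PGD.

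The cost is a few sentences. Sample size, visits and data collection stay as they are, and the model needs only its time coding stated. The one real downside is that a benefit confined to the early months becomes a secondary result.
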